## 1. Introduction

The somatotrophic axis regulates many essential physiologic functions. Although growth hormone (GH) was originally recognized for its primary role in effecting growth in stature, its importance in preserving anabolism and its involvement in tissue repair during adulthood have recently been more fully documented. The aging process, however, is associated with a blunting of basal and stimulated GH secretion. This early and progressive decrease in spontaneous GH secretion is associated with a decrease in blood levels of insulin-like growth factor 1 (IGF-1), the principal effector and marker of GH anabolic actions.

Experimental attempts to restore complete functionality of the somatotrophic axis in aged patients have included the administration of exogenous recombinant human growth hormone (rhGH) and analogues of growth hormone releasing factor (GRF). Administration of rhGH to these patients, however, has been associated with a variety of adverse effects including hyperglycemia, insulin resistance, fluid retention, carpal tunnel syndrome, and gynecomastia. These adverse effects have been shown to be more frequent in patients with the highest IGF-1 levels. Importantly, the IGF-1 negative feedback on GH secretion is inoperative during treatment with exogenous rhGH, and exogenous rhGH is unable to mimic the physiologic, pulsatile rate of endogenous GH secretion. While GRF is able to preserve the physiologic pulsatile pattern of GH secretion, rapid hydrolysis of natural GRF by dipeptidyl-amino peptidase in serum limits its efficacy as a treatment modality. Administration of a GRF analogue has been associated with enhanced insulin sensitivity in males, in contrast to the insulin resistance observed with the administration of rhGH.

TH9507, a GRF analogue being developed by Theratechnologies Inc., includes the natural 44 amino acid sequence of human GRF (hGRF), on which a hexenoyl moiety (a C6 chain with a double bond on position 3) has been anchored on Tyr 1 at the N-terminus part of the molecule. The presence of this hydrophobic side chain is believed to provide steric hindrance that prevents or delays the coupling of dipeptidyl-amino peptidase to TH9507, resulting in enhanced stability in serum. In fact, the plasma half-life of TH9507 was estimated to be 8 hours (*in vitro*) in comparison to hGRF, which was degraded in minutes. In a Phase 1b study TH9507 increased IGF-1 levels in healthy older men to levels typically observed in young adults. Since TH9507 has the natural sequence of GRF and is relatively resistant to degradation by peptidases in serum, it combines three key features for optimal efficacy and safety in aged patients: specificity on GH secretion; induction of GH secretion in a pulsatile, physiologic manner; and a powerful effect on IGF-1 secretion. These characteristics are expected to translate into clear clinical benefits in a number of targeted therapeutic indications.

## 1.1 Rationale

The clinical development program for TH9507 includes its use in patients who could benefit from enhancement of anabolic effects, including patients with COPD, hip fractures, and other age-related disorders associated with somatopause. As noted, different changes in insulin sensitivity have been observed with rhGH and GRF analogue administration. It is anticipated that a number of patients to be enrolled in future trials of TH9507 will have glucose intolerance and/or overt diabetes. Therefore, the purpose of this study is to investigate the safety of daily administration of TH9507 in patients with type 2 diabetes mellitus, in particular, the potential for effects on insulin sensitivity and diabetic control.

## 2. Study Objectives

The primary objective will be to evaluate the safety of two doses of TH9507 administered over 12 weeks by daily subcutaneous injections in patients with stable type 2 diabetes.

## 3. Investigational Plan

### 3.1 Overall Study Design

This is a randomized, double-blind, placebo-controlled, parallel group, multicenter study of two doses of TH9507 (1 mg and 2 mg) administered daily by subcutaneous injection for 12 weeks.

After screening and a 14-day lead-in period, subjects will be randomized by insulin use (see Section 4.1.6) to one of three treatment groups. Subjects will be evaluated after 1, 4, 8, and 12 weeks of treatment and at a follow-up visit at Week 16.

The study schematic is presented in Figure 3.1-1.

Figure 3.1-1 Study Schematic

[figure not shown]

### 3.2 Discussion of Design

This study will incorporate a two-week lead-in period prior to randomization for the purpose of establishing and characterizing daily dietary patterns and daily blood glucose measurements prior to the randomization visit. Further, the lead-in period will provide patients with the opportunity to become accustomed to required study procedures such as the completion of a diary to monitor diet, exercise, blood glucose, and hypoglycemic episodes. The duration of 12 weeks of treatment is adequate to discern important changes in glycosylated hemoglobin (HbA1c).

### 3.3 Study Population

#### 3.3.1 Patient Population

A total of approximately 45 patients with stable type 2 diabetes on stable diabetes treatment regimen (receiving oral hypoglycemics with or without insulin) will be enrolled into the study. Fifteen (15) subjects will be randomized to each treatment group to ensure that approximately 13 subjects per group complete the study. After 33 patients have been randomized based on insulin use (insulin use or non-insulin use), enrollment may be halted for that group but continued in the other group.

### 3.3.2 Inclusion and Exclusion Criteria

#### **Inclusion criteria**

1. Male or postmenopausal or surgically sterilized female subjects, of 50 years of age or older;
2. Documented diagnosis of type 2 diabetes as defined by the American Diabetes Association;
3. Diagnosis of type 2 diabetes for at least 3 months prior to screening;
4. Subjects on stable diabetes treatment regimen (receiving oral hypoglycemics with or without insulin) for at least 2 months prior to screening;
5. Screening and pre-randomization HbA1c <10.0%, according to central laboratory;
6. Subjects with a Body Mass Index between 25 and 38 kg/m^2.  
(BMI = Weight [kg] ÷ {Height [m]});
7. Subjects willing to perform specified home blood glucose monitoring and comply with all study protocol requirements;
8. Signed informed consent.

#### **Exclusion criteria**

1. Serum creatinine >2 mg/dL;
2. Fasting triglyceride >1000 mg/dL;
3. Albuminuria >200 mcg/24 hours (this assessment may be obtained during the lead-in period);
4. Positive mammography (if female) or prostate-specific antigen (PSA) or prostate examination for cancer (if male);
5. Donation of blood during the 30 days prior to the screening visit. Donation of blood is also prohibited during the study;
6. Use of oral or parenteral glucocorticoids in the 30 days prior to screening;
7. Use of any experimental or marketed growth hormone (GH), GH secretagogues (e.g., growth hormone releasing factor (GRF) products), IGF-1, or IGFBP-3 during the previous 6 months;
8. Subjects with two or more severe hypoglycemia episodes within the past 6 months, or any hospitalization or emergency room visit due to poor glycemic control within the past 6 months. Similarly, during the lead-in period, any subject with more than one severe hypoglycemic episode or any hospitalization or emergency room visit due to poor glycemic control will be excluded from randomization;
9. History of or presence of active concomitant conditions or diseases (e.g., myocardial infarction, poorly controlled hypertension, thyroid disease, rheumatoid arthritis, seizure disorder, diabetic neuropathy, diabetic retinopathy [except patients

with only microaneurysms on fundus examination]) that would interfere with the protocol conduct and endpoint measurements;

10. Subjects with a major surgical operation during the 30 days prior to screening;
11. Subjects with known hypopituitarism, history of pituitary tumor/surgery, head irradiation, or severe head trauma.
12. Current cancer or history of cancer, except non-melanomatous skin cancer;
13. Subjects with active infection at any body site or a history of severe infection (requiring oral or parenteral treatment) during the 30 days prior to screening;
14. Subjects with drug or alcohol dependence or abuse;
15. Subjects with clinically significant abnormalities on screening laboratory evaluation (unless discussed with and approved by the medical monitor);
16. Subjects with allergy to synthetic growth hormone products or their excipients;
17. Subjects who have previously received growth hormones in any clinical trial; and
18. Participation in a trial of an experimental drug or device within 90 days prior to screening.

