##### VISIT 1: (Week -3, Screening)

- Obtain signed informed consent.
- Review inclusion and exclusion criteria.
- Obtain medical history.
- Review concomitant medications.
- Perform physical/neurological examinations (including screening for diabetic sensory neuropathy).
- Obtain 12-lead electrocardiogram.
- Obtain Vital signs (blood pressure, respiratory rate, pulse rate).
- Obtain body weight.
- Calculate body mass index.

- Perform funduscopy with dilation by optometrist or ophthalmologist (may be performed during the lead-in period) and examine for evidence of diabetic retinopathy (microaneurysms will not exclude the patient from participating in the study).
- Obtain blood for clinical laboratory screening tests (hematology, blood chemistry, lipid profile, and urinalysis-subjects with minimal proteinuria [ $<2+$ ] may continue with screening).
- Obtain blood for glycosylated hemoglobin (HbA1c) and insulin antibodies.
- Schedule mammography (for females) and prostate examination/PSA (for males) if not done within six months of screening.
- Collect 24-hour urine for albumin (may be performed during the lead-in period).
- Schedule Visit 2 to occur 6-8 days following Visit 1.

VISIT 2: (Week  $-2 \pm 1$  day, Start of lead-in period)

- Review inclusion and exclusion criteria.
- Assess adverse events.
- Review concomitant medications.
- Obtain body weight.
- Obtain vital signs (BP, RR, PR).
- Dispense diary (to monitor home blood glucose measurement, hypoglycemic episodes, study drug administration, **adjustments in oral hypoglycemic agents and/or insulin dosage**, diet, and exercise) and provide instructions regarding completion of the diary.
- Dispense home glucose meter with instructions.
- Dispense boxes of strips and lancets.
- Instruct the subject to withhold oral sulfonylurea, insulin, and other insulin secretagogues but he/she may take oral non-sulfonylurea hypoglycemic medication (if oral insulin sensitizer) in the morning of Visit 3.
- Instruct the subject to collect urine the day before the scheduled visit (starting at 6AM) until the morning (6AM) of the clinic visit.
- Dietician interview and assessment – caloric intake assessment, skin thickness (Harpenden), waist/hip measurements, and body fat mass (Lange).
- Schedule Visit 3 to occur 12-16 days after Visit 2.

VISIT 3: (Week  $0 \pm 2$  days, Baseline and Randomization)

- Review inclusion/exclusion criteria.
- Assess adverse events.
- Review concomitant medications.

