#### 3.5.2.3.4 24-Hour Quantitative Urine Tests

Albumin, creatinine, nitrogen, and total urine volume

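### The albuminuria exclusion is written as 200 mcg per 24 hours (0.2 mg/day); the unit is probably wrong, and applied literally it would exclude nearly every candidate

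*Protocol*

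**What the plan says.** Three places in the Protocol bear on urinary albumin or protein at entry.

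- Section 3.3.2, exclusion 3: "Albuminuria >200 mcg/24 hours (this assessment may be obtained during the lead-in period".
- Section 3.5.1, Visit 1, on the screening urinalysis: "urinalysis-subjects with minimal proteinuria [ $<2+$ ] may continue with screening". A separate item at the same visit is "Collect 24-hour urine for albumin (may be performed during the lead-in period".
- Section 3.5.2.3.4, the quantitative urine tests: "Albumin, creatinine, nitrogen, and total urine volume". No unit or reference range is attached.

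Exclusion 1 is the companion renal criterion, "Serum creatinine >2 mg/dL". Section 3.3.1 sets the enrolment that these criteria have to allow: "A total of approximately 45 patients with stable type 2 diabetes on stable diabetes treatment regimen". Section 4.1.6 randomizes only patients who satisfy all the entry criteria. Exclusion 15 lets the medical monitor approve certain laboratory abnormalities, but that allowance belongs to item 15 and is not attached to exclusion 3.

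**The concern.** A limit of 200 micrograms over a whole day is very small for a 24-hour albumin collection. It also sits oddly beside its neighbours. The Visit 1 list tolerates some protein on the urinalysis, and exclusion 1 tolerates serum creatinine up to 2 mg/dL, yet exclusion 3 tolerates almost no albumin.

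The criterion applies to every subject and has no stated waiver. A site that follows it literally would turn away nearly everyone once the 24-hour result arrives. A site that randomizes such subjects anyway would record an unmet entrance criterion each time (the first deviation category in section 4.1.11), and genuine eligibility failures would be hard to find among them. A site that guesses the intended unit applies a renal limit that the protocol does not state. This is a safety study in patients with type 2 diabetes, so the renal entry screen should be readable in only one way.

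**Working it through.** **Inputs from the Protocol**

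- Limit: 200 mcg per 24 hours (section 3.3.2, exclusion 3).
- Measurement: a 24-hour urine collection (section 3.5.1, Visit 1; section 3.5.2.3.4).
- Planned enrolment: about 45 (section 3.3.1).

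**Assumptions, not in the Protocol**

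- Normal albumin excretion: 1 to 30 mg/day.
- Urine volume: 0.5 to 3 L/day.
- Protein concentration at a trace to 1+ dipstick reading: 10 to 30 mg/dL.

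The limit is a stated value, not a derived one, so there is no calculation of the plan's own to reproduce. The check is unit conversion.

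**Step 1. The limit in mg/day.** 200 mcg / 1000 = 0.2 mg per 24 h. As a concentration this is 0.2 / 0.5 = 0.4 mg/L at the smallest assumed volume and 0.2 / 3 = 0.07 mg/L at the largest.

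**Step 2. Against assumed normal excretion.** Ratio = excretion / 0.2.

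| Assumed excretion (mg/day) | Multiple of the limit |
|---|---|
| 1 | 5 |
| 5 | 25 |
| 10 | 50 |
| 30 | 150 |

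Even the lowest assumed value is five times the limit, so the conclusion does not depend on where in the range a subject falls.

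**Step 3. Against the Visit 1 allowance.** Daily protein = concentration (mg/dL) × 10 × volume (L).

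- Lowest case: 10 × 10 × 0.5 = 50 mg/day, and 50 / 0.2 = 250 times the limit.
- Highest case: 30 × 10 × 3 = 900 mg/day, and 900 / 0.2 = 4500 times the limit.

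These figures are for total protein, and the criterion is on albumin. In the lowest case, though, albumin would need to make up only 0.2 / 50 = 0.4% of the protein to reach the limit. On these assumptions, nearly every subject whom the Visit 1 allowance keeps in screening would then fail exclusion 3.

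**Step 4. How far the unit matters.**

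- Mass unit changed, 200 mg/24 h: 200 / 0.2 = 1000 times the written limit.
- Time base changed, 200 mcg/min: 200 × 1440 / 1000 = 288 mg/24 h, and 288 / 0.2 = 1440 times the written limit.

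These two readings differ from each other by 288 / 200 = 1.44, that is 44%. They are shown for scale only.

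**Step 5. Does another section settle the unit?** No. Section 3.5.2.3.4 lists albumin without a unit, and the Visit 1 item names the collection without a limit. A unit slip is credible, because another laboratory limit in the same protocol is inconsistent: triglyceride is 1000 mg/dL in exclusion 2 and 1000 mg/L among the discontinuation reasons in section 3.3.3. Those two entries also need reconciling.

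**The case against.** The strongest reply has several parts.

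**The two urine rules do not contradict each other.** A reader might infer that exclusion 3 and the Visit 1 rule cannot both hold. The Protocol does not support that. The Visit 1 wording only lets a subject go on with screening; it does not make the subject eligible. The 24-hour albumin is a separate test that may come later, so a subject can pass the first and fail the second. This objection stands. What remains is a practical conflict, because the allowance achieves almost nothing if the later limit is 0.2 mg/day.

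**The multiples rest on outside figures.** The Protocol contains no normal range, dipstick scale or urine volume. This stands too: the multiples are conditional on the stated assumptions. The direction is not sensitive to them, since even 1 mg/day is above the limit.

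**The time base may not be the culprit.** A reader might conclude that a per-minute limit was mistyped. A wrong mass unit fits equally well, and the text does not decide between them.

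**The harm to the analysis is conjecture.** A reader might infer that sites would choose different cut-offs and so distort the center term. Nothing in the Protocol shows that they would, and sections 4.1.4 and 4.1.14 adjust for center in order to separate it from treatment. The primary endpoint, hypotheses and sample size do not use this criterion, and the serum creatinine limit remains as a second renal screen.

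**A literal reading would be noticed at the first results.** That is likely, and it makes silent bias less probable. It does not make the criterion usable: sites would still have to wait for a correction or improvise.

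**Conclusion.** Exclusion 3 is wrong as written. The stated limit is 0.2 mg of albumin per day. On an assumed normal excretion of 1 to 30 mg/day it is exceeded 5 to 150 times, so it would exclude nearly every candidate and cannot be squared with enrolling about 45 patients. The conversion to 0.2 mg/day follows from the text alone. The statement about who would be excluded rests on the assumed range but holds across all of it.

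The probable cause is a unit error of about three orders of magnitude, in the mass unit or in the time base. The Visit 1 proteinuria allowance is left with almost no practical effect, which is further evidence that the limit was not meant to be this low; it is not a formal contradiction. The point concerns eligibility only and changes no sample size or power figure.

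**What to change.** The sponsor should verify the unit of exclusion 3 against the intended limit and correct it. The limit should then be stated once, in the unit reported by the laboratory that assays the 24-hour collection. The Protocol names a central laboratory for HbA1c and for the glucose tolerance samples. For assays generally, section 3.5.2.3 speaks only of approved laboratories, so the reporting unit should be confirmed and not presumed. The corrected limit and the Visit 1 proteinuria rule must be reconciled so that their relation is clear. Which value is right is for the sponsor to decide, and none is proposed here.

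The cost is about one line in a protocol amendment. The 24-hour albumin collection is already planned, so no procedure is added.

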### 3.4. Treatment

#### 3.4.1 Investigational Drug and Reference Therapy

Active drug and placebo will be provided as lyophilized powder in vials of identical appearance and supplied in blister cards at each monthly visit. The active drug is supplied as 1.1 mg of TH9507 (peptide content) with 55 mg of mannitol. The placebo is composed of 55 mg of mannitol. The study drugs will be supplied as follows:

| Dose | No. of Vial of Active Drug
(A) | No. of Vial of Placebo
(B) |
|-------------|-------------------------------------------|---------------------------------------|
| 1 mg        | 1 vial of 1.1 mg active drug              | 1 vial of mannitol                    |
| 2 mg        | 2 vials of 1.1 mg active drug             | -                                     |
| Placebo     | -                                         | 2 vials of mannitol                   |

Each vial will be reconstituted with 1.1 mL of sterile water for injection (provided by the sponsor). One mL of each preparation is then taken out of each vial using a 3-mL syringe. The total volume will be 2 mL. The preparation is then injected subcutaneously.

The lyophilized vials will be kept at -20°C at the investigational sites. The supplies of study drug dispensed to the subjects will be kept refrigerated between 2°C and 8°C at the subject's home for daily reconstitution and use.

Subjects will self-inject 2 mL of study drug subcutaneously (using 1 mL each from vial A and vial B) at rotating sites every morning at 9:00AM  $\pm$  3 hour, (i.e., between 6AM and noon). The subject may elect to have a family member or a health professional administer the study drug. The study drug may be administered in either one or two subcutaneous injections at each dosing time at one or two sites. The study drug will be administered at the General Clinical Research Centers (GCRCs) at Visits 3, 4, 5, and 6.

Medication labels will comply with the regulatory requirements.

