### 3.5.2 Safety Assessments

This is a study to assess the safety of 12 weeks of daily administration of TH9507. Safety assessments will include the monitoring and recording of all adverse events and any serious adverse events; the sequential assessment of hematology, blood chemistry, and urinalysis parameters; the monthly monitoring of HbA1c, periodic assessments of lipid profiles, including HDL, LDL, total cholesterol, and triglycerides; monitoring for antibodies to TH9507 before and after 12 weeks of treatment; and periodic measurements of blood pressure, as well as performance of physical examinations including screening testing for diabetic sensory neuropathy. This study will seek to assess any clinically meaningful changes in insulin sensitivity through use of sequential periodic oral glucose tolerance tests with paired insulin and glucose levels to determine insulin:glucose ratios.

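### The allergy exclusion names growth hormone products, which nobody in the trial receives, and does not on its wording cover TH9507 or other GRF products

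*Protocol*

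**What the plan says.** Four exclusion criteria in protocol Section 3.3.2 bear on allergy or earlier exposure.

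- Exclusion 16 (allergy): "Subjects with allergy to synthetic growth hormone products or their excipients".
- Exclusion 17 (exposure in a trial, no time limit): "Subjects who have previously received growth hormones in any clinical trial".
- Exclusion 7 (any use, experimental or marketed, time-limited): growth hormone and, as a further item, "GH secretagogues (e.g., growth hormone releasing factor (GRF) products), IGF-1, or IGFBP-3 during the previous 6 months".
- Exclusion 18 (any experimental product): "Participation in a trial of an experimental drug or device within 90 days prior to screening".

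The product is described elsewhere. Section 1 introduces "TH9507, a GRF analogue being developed by Theratechnologies Inc". Section 3.4.1 states "The active drug is supplied as 1.1 mg of TH9507 (peptide content) with 55 mg of mannitol" and "The placebo is composed of 55 mg of mannitol". Its supply table gives every arm two vials per day: one active and one placebo for 1 mg, two active for 2 mg, and two placebo for the control arm.

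Section 3.5.2 lists among the safety assessments "monitoring for antibodies to TH9507 before and after 12 weeks of treatment".

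**The concern.** An allergy exclusion is there to keep out people with a known reaction to what they will be given. This one is written around a class of product that no arm contains. Safety is the trial's primary objective (Section 2), dosing is daily for 12 weeks, and most injections are given at home by the subject or a helper. A site that applied exclusion 16 exactly as written would ask about growth hormone and would not have to ask about GRF products or TH9507.

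The earlier-exposure criteria show the same substitution. Exclusion 17 has no time limit but names growth hormones only. If it was meant for the study drug's own class, it does not say so, and someone exposed to TH9507 long ago could enter. That bears on how a positive antibody result would be read.

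**Working it through.** The check is a literal reading of the criteria against the product description, with a little arithmetic on exposure.

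**Step 1. Does growth hormone, as this protocol uses the term, include the study drug?** Exclusion 7 names growth hormone, then GH secretagogues with GRF products as the example, as distinct entries. Section 1 contrasts exogenous growth hormone with GRF and its analogues on feedback, pulsatility and insulin sensitivity, and Section 1.1 builds the rationale partly on that contrast. By the document's own usage the answer is no.

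**Step 2. What is injected?** Mannitol per day, from Section 3.4.1:

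- Reconstituted: 2 vials × 55 mg = 110 mg, in every arm.
- Injected: 1 mL is drawn from each vial made up with 1.1 mL, so 110 × (1 / 1.1) = 100 mg, taking the reconstituted volume as 1.1 mL.

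Subjects receiving TH9507: 2 arms × 15 = 30 of 45. Subjects receiving growth hormone: 0 of 45.

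**Step 3. Apply the criteria case by case.**

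| Candidate | Excl. 7 | Excl. 16 | Excl. 17 | Excl. 18 | Result on the wording |
|---|---|---|---|---|---|
| Known allergy to TH9507 or a GRF product, no recent use | no | no | no | no | not excluded |
| Known allergy to mannitol | no | unclear | no | no | cannot be settled |
| TH9507 or other GRF in a trial, within the last 6 months | yes | no | no | if within 90 days of screening | excluded |
| TH9507 or other GRF in a trial, 7 months ago | no | no | no | no | not excluded |
| Growth hormone in a trial, at any time | if within 6 months | no | yes | if within 90 days of screening | excluded |

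The mannitol row is unclear because the excipients in exclusion 16 are those of growth hormone products, and the protocol does not say what those are.

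**Step 4. Does the antibody sampling close the gap?** Visit 1 draws insulin antibodies but not TH9507 antibodies. TH9507 antibody serum is first drawn at Visit 3, the visit at which the subject is also randomized and given the first dose, and no eligibility criterion uses the result. It is drawn again at Visit 7. The baseline sample can therefore show pre-existing antibodies when the data are analysed, but it cannot keep the subject out.

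**Step 5. Scale.** With 15 subjects per arm, one subject is 1/15 = 6.7% of an arm. This is only the weight of a single case. The protocol gives no rate of GRF or mannitol allergy and no count of earlier TH9507 recipients, so no expected number can be calculated.

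**The case against.** The case against making much of this is substantial, and most of it stands.

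- **Recent exposure is already covered.** A reader might infer that anyone earlier given TH9507 can enter, or that the study drug has the loosest exposure rule. Neither is so. Exclusion 7 bars GRF products for 6 months, the same period as for IGF-1 and IGFBP-3 and longer than the 90 days for experimental products in general. Only exposure more than 6 months earlier passes.
- **Exclusions 7 and 17 do not contradict each other.** One sets a 6-month limit on any use and the other adds an unlimited bar for growth hormone given in a trial. A site can apply both. Nothing in the protocol says that 6 months is too short for GRF products, so a longer bar would be a design preference.
- **Mannitol may be covered.** It is tempting to say that mannitol allergy is not excluded. The phrase about excipients leaves this open.
- **The antibody results are not simply spoiled.** The Visit 3 sample lets detectable pre-existing antibodies be separated from new ones, and antibodies are neither the primary nor a secondary endpoint in Section 4.1.1.
- **Few candidates are likely to be affected.** The earlier human studies of TH9507 that the protocol cites were in healthy volunteers, including healthy older men, whereas this trial requires type 2 diabetes on stable treatment. Overlap should be small, although no figure is given.
- **Investigators might exclude a known allergy anyway**, perhaps under exclusion 9, which covers conditions that interfere with conduct. That relies on discretion and does not mention allergy.

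None of these points answers the central one: the criterion written for allergy names the wrong class of product.

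**Conclusion.** The point holds in a limited form. Exclusion 16, on its wording, screens for allergy to products given to none of the 45 planned subjects. It does not name the GRF analogue given to 30 of them or the mannitol given to all of them. It does not cover known allergy to TH9507 or GRF products, and its reach to mannitol is unclear. Exclusion 17 leaves it uncertain whether its unlimited bar was intended for the study drug's class; as written, TH9507 or other GRF exposure more than 6 months earlier is not barred.

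This rests on two assumptions: that sites apply the criteria as written, and that growth hormone means in exclusions 16 and 17 what it means in exclusion 7.

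A reader might go further and infer that the safety or antibody results would be materially biased. The documents do not support that: they give no frequency for any of these cases, and a baseline antibody sample is taken. No sample size, power, type I error or primary endpoint figure changes. This is a wrongly worded safety criterion that is cheap to correct.

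**What to change.** Reconcile exclusion 16 with Sections 1 and 3.4.1 so that the allergy criterion addresses the substances actually injected and is explicit about mannitol. Ask the sponsor to confirm whether growth hormones in exclusion 17 was meant to include the study drug's class, and to word it accordingly. Which exposure rule should apply is the sponsor's clinical decision; the request is that the text state it clearly.

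The cost is a line or two of protocol text. The criteria can be checked from the medical history already taken at Visit 1, so no visit, sample or analysis is added. The downside is possibly a rare extra screen failure.
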